## Abstract

**Background:**

Stroke patients are often affected by arm paresis, have functional impairments and receive help from professional or informal caregivers. Progressive resistance training is a common intervention for functional impairments after paresis. Randomised controlled trials (RCT) showed benefits for functional recovery after resistance training. However, there is a lack of evidence for strength training in subacute stroke patients. The aim of this study is to investigate safety and effectiveness of arm strength training in subacute stroke patients.

**Methods:**

We will conduct a prospective, assessor-blinded RCT of people with subacute stroke. We will randomly assign patients to one of two parallel groups in a 1:1 ratio and will use concealed allocation. The intervention group will receive, in addition to standard treatment, high-intensity arm training (three times per week, over three weeks; 60 min each session; with a total of nine additional sessions). The control group will receive, in addition to standard treatment, low-intensity arm training (same quantity, frequency and treatment time as the intervention group). Standard treatment for the affected arm includes mobilisation, stretching, therapeutic positioning, arm and hand motor training, strengthening exercises, mechanical assisted training, functional training and task-oriented training. The primary efficacy endpoint will be grip strength. Secondary outcome measures will be Modified Ashworth Scale, Motricity Index, Fugl-Meyer Assessment for the upper limb, Box and Block Test and Goal Attainment Scale for individual participatory goals. We will measure primary and secondary outcomes with blinded assessors at baseline and immediately after three weeks of additional therapy. Based on our sample size calculation, 78 patients will be recruited from our rehabilitation hospital in two and a half years. Drop-out rates and adverse events will be systematically recorded.

**Discussion:**

This study attempts to close the evidence gap for effects of arm strength training in subacute stroke patients. The results of this trial will provide robust evidence for effects and safety of high-intensity arm training for people with stroke.

**Trial registration:**

German Clinical Trials Register, DRKS00012484. Registered on 26 May 2017.

**Electronic supplementary material:**

The online version of this article (10.1186/s13063-019-3261-3) contains supplementary material, which is available to authorized users.

## Background

Stroke patients are often affected by decreased strength and functional impairments [1]. Paresis of the upper limb occur in 77% of the cases [1]. Muscle weakness affects activities of daily life (ADL), therefore, writing or grasping a glass of water can be difficult or even impossible [2, 3]. People with stroke often suffer from long-term impairment; consequently, after discharge from hospital, 41% of them need help for ADL and 20% receive nursing at home by family members or friends [4].

Recent studies have shown that interventions like constraint-induced movement therapy (CIMT), mirror therapy, training with virtual reality, or repetitive task training are effective to improve upper-limb function after stroke [5]. It is necessary to learn more about the effectiveness of different interventions and training methods in arm rehabilitation to increase the independence of people with stroke. The selection of training methods can be based on individual needs of patients or on their effects and the training target. Early studies showed that a greater dose of an intervention (which means the number of repetitions or the duration of intervention) seems to be an advantage for functional recovery after stroke [5]. A large amount of intervention minutes or number of repetitions are effective to increase arm function [6] and ADL [7]. There are several possibilities to vary intensity of training, e.g. through using different numbers of repetitions, various complexity of tasks, different feedback modalities, or additional weights.

Prange et al. compared robotic weight-supported arm training with a conventional training in subacute stroke patients to examine training effects on arm function and perceived motivation [8]. The robotic arm training obtained similar effects to the comparison group but with higher motivation. A higher perceived motivation can be used to increase treatment intensity or dose. In contrast to Prange et al., we will focus on effects of arm training on strength and instead of robotic weight-supported training we will use additional weight loads to increase intensity of intervention.

Chan et al. found in a single-group cohort study that weight-supported training with robotic devices can increase arm function, especially in subacute stroke patients with moderate or severe impairments [9]. The more severely affected the patients, the higher the improvements. It is unclear if robotic arm training has an advantage to another intervention type because there is no comparison group. The training effects are different in patients with mild, moderate, or severe impairments but we do not know if all these patients can train with additional weights, no matter how severe the impairments are.

Randomised controlled trials (RCT) found that resistance training for the upper limb that uses additional weights for a higher training intensity increased strength [10, 11], arm function [12–15] and arm activities [14] in chronic stroke patients. Three studies searched for adverse events (AE) after arm strength training in chronic stroke patients. Two of these found no AEs [16, 17] and one reported muscle soreness [15]. Only two studies examined treatment effects of such intensive and progressive arm training in subacute stroke patients [17, 18]. Donaldson et al. found that additional functional resistance training leads to greater improvements of arm function than standard treatment or double dose of standard treatment [18]. In this pretest–post-test clinical trial, no between-group comparisons were performed. Thus, there is no information about a possible advantage for one of the interventions in subacute stroke patients. Winstein et al. compared a control group which performed five times per week functional training with an intervention group which performed a combination of three times resistance training and two times functional training per week [19]. Mild affected stroke patients of the intervention group showed greater improvements of arm function (measured with the motor subscore of the Fugl-Meyer-Assessment for upper extremity) than the control group. There were no group differences in other functional assessments, e.g. grip strength. This study is limited by non-blinded assessors. Only these two studies investigated resistance training with additional weights in the first three month after stroke. AEs in patients in the subacute phase after stroke were not examined. This evidence related to the effectiveness of strength training (resistance training) in improving upper limb function and activities is insufficient. A solid evaluation of intensive resistance arm training in the subacute phase after stroke is not possible. It is important to investigate common interventions early after stroke to follow the recommendations of an early start to the training. An early start to the training (one week after stroke onset) with higher treatment dose speeds up the functional recovery of arm activities [20, 21]. The highest rise of recovery is achieved in the first weeks after stroke with the major part of recovery already reached at this point [20, 22]. However, less is known about which therapeutic interventions could support this early recovery. Strength training for preservation or improvement of muscle strength is recommended in stroke guidelines [23, 24]. Despite the lack of evidence for therapeutic effects and AEs in subacute and early chronic stroke patients, resistance training is recommended [25] and used in rehabilitation.

We want to compare intensive resistance arm training with low-intensity arm training in the subacute phase after stroke. We developed a training program possibly feasible for patients with mild to severe stroke. We will examine if a three-week training programme is safe and effective for these patients.

### Objective

We will use a parallel-group RCT design to assess the safety and the effects of arm strength training in persons with subacute stroke. The control group performs the same exercises with low intensity. We will evaluate arm function, activities, participation and AEs.

## Methods

### Study design

This is an assessor-blinded, parallel-group, single-centre RCT of people with upper limb paresis after stroke (see Fig. 1). Stroke was defined as ‘rapidly developing clinical signs of focal (or global) disturbance of cerebral function, with symptoms lasting 24 hours or longer […], with no apparent cause other than of vascular origin’ [26] diagnosed by a neurologist and confirmed by computer tomography or magnetic resonance imaging.

**Fig. 1 Fig1:**
[figure not shown]
*Flow diagram* of study design

The study is conducted at the neurological rehabilitation hospital Asklepioskliniken Schildautal Seesen in Germany. Before the intervention, patients will be randomised in a 1:1 ratio into one of two intervention parallel groups.

The first experimental group will receive, in addition to standard treatment, intensive upper limb strength training with an intensity of 80% of the maximum force (three times per week, over three weeks, 60 min per session, with a total of nine additional sessions). The other group will receive, in addition to standard treatment, functional arm training with an intensity of 40% of the maximum force (with the same quantity, frequency and treatment time as the intervention group). After receiving ethical approval and registration of the study, we started recruiting in our hospital in May 2017. The final assessments will be made in 2018. The study protocol is prepared according to the SPIRIT Statement (http://www.spirit-statement.org/) [27] (see Additional file 1; for the SPIRIT figure, see Fig. 2).

**Fig. 2 Fig2:**
[figure not shown]
Schedule of enrolment, interventions and assessments. Time points: -t1: before baseline screening; t0: baseline; t1: 3 weeks after treatment. MAS Modified Ashworth Scale, MI Motricity Index, FMA-UL Fugl-Meyer Assessment for the upper limb, BBT Box and Block Test, GAS Goal Attainment Scale

### Screening process

Patient lists will be searched for potential study participants daily. We will enter all patients with the diagnosis of stroke into our screening log. Subsequently, the patient will be screened for eligibility (Fig. 2) with the inclusion and exclusion criteria as outlined in Table 1. We will fully inform eligible patients and/or their caregivers about the study; in addition, we will assign an identification number to the patient. Patients and/or their caregivers are then asked to provide informed consent. If a potential participant does not meet the inclusion criteria, we will not retain identifiable information on that patient. We will report all reasons for exclusion in a flow chart. After providing informed consent, we will record all medical and neurological information at baseline in a case report form. All baseline assessments will be conducted by an occupational therapist or a physiotherapist. Those study assessors will not be involved in treating patients or with administration of the intervention and will remain fully blinded to the patient’s group allocation throughout the whole trial.

**Table 1 Tab1:** Inclusion and exclusion criteria

Inclusion criteria	
1. Participant is in the subacute phase after having a stroke (within 3 months after stroke) 2. Participant has a Barthel Index of at least 30 points 3. Participant has an arm paresis with a Medical Research Council score of 2–4 points for shoulder abduction, elbow flexion and finger flexion 4. Participant is aged > 18 years 5. Participant can lift the affected hand from their lap to a desk standing in front of them 6. Participant is able to sit for 30 s without using upper extremities for support 7. Passive range of motion is at least 90° of shoulder abduction and flexion; 90° of elbow flexion; 30° of wrist extension; 30° between pronation and supination; a touch of finger tips and thumb and submaximal finger extension is possible 8. Apraxia Screen of TULIA Score of ≥ 5 9. Written informed consent of the patient or their legal guardian has been obtained	
Exclusion criteria	
1. 4 or 5 points on Modified Ashworth Scale 2. > 5 points on a pain rating scale at rest 3. Manifest heart diseases like cardiac insufficiency (> New York Heart Association stage 1), angina pectoris, myocardial infarction within 120 days before recruitment, cardiomyopathy, hypertonia (European Society of Hypertension, grade 2 [47]) or severe cardiac arrhythmia 4. Inflammation or infection, with fibre, ECOG Performance Status Grade 3 or 4 [48] or isolation 5. Myopathy (like muscular dystrophy, myasthenia gravis or myotonia)	

### Informed consent

Written informed consent for study participation will be obtained 1–7 days after screening for eligibility. Participants will be informed that successful completion of the baseline tests is required before randomisation to an intervention group.

### Eligibility criteria

The diagnosis of stroke will be confirmed by a neurologist before admission to our neurological rehabilitation hospital. A previous stroke is no reason for exclusion. Participants will be in the subacute phase (within three months after stroke) and will have a Barthel Index (BI) of at least 30 points. If the BI is 85–100 points (mild stroke), the patient will be included at least 24 h after stroke. If the BI is < 85 points (moderate stroke) the patient will be included at least seven days after stroke. They will be able to sit free for 30 s (sitting balance score of at least 2 points) and they will be able to lift the affected hand from their lap to a desk standing in front of them. They will have a Medical Research Council Score of 2–4 for shoulder abduction, elbow and finger flexion. The passive range of motion (ROM) will allow a touch of finger tips and thumb as well as submaximal finger extension. Patients will achieve an Apraxia Screen of TULIA Score of ≥ 5 (for details, see Table 1).

### Assessment of safety and adverse events

During the training, the examiner monitored heart rate (HR) and rating of perceived exertion (RPE) according to Borg’s 20-point scale [34, 35]. Different intervention types in stroke rehabilitation have an impact on the cardiorespiratory system [36]. HR monitoring can be used to measure cardiorespiratory responses during training [36, 37]. The maximal HR during training should not be higher than the age-predicted maximal HR of 220 minus age to avoid physical stress [38]. We will monitor HR to assess training effects on the cardiorespiratory system and to avoid cardiovascular stress caused by training. In addition to the HR, the subjective exertion sensation should be assessed with the Borg Perceived Exertion Scale to prevent severe physical stress [39, 40]. The rating of perceived exertion allows conclusions about training intensity [41]. For example, a perceived exertion of 16 points represents a training intensity of 80% of the one repetition maximum and 10 points represents an intensity of 40% of the one repetition maximum. Thus, this information can be used to monitor training intensity and to check if the intensity exceeds the expected 16 points Borg’s rating of perceived exertion scale.

There is a risk for heavy physical strain or shoulder pain of the hemiparetic arm due to a high weight load in strength training. In order to ensure the safety of the study participants, the following risk-management processes will be performed:We will follow clearly defined eligibility criteria to include only patients who do not have severe heart diseases or have pain in the affected arm.We will periodically monitor HR and rating of perceived exertion during the training.The training will be guided by qualified staff (physiotherapists).AEs such as self-reported fatigue, a decline in performance of 30%, pain, dizziness, amentia or impaired consciousness, sickness, dyspnoea, tinnitus, angina pectoris, muscle soreness, swelling and decrease in compliance to training will be continuously recorded.

After each intervention, the treating physiotherapist will record the presence of AEs. During the intervention phase and at the final assessment the following parameters will be systematically recorded: cardiovascular or cerebrovascular events; referral to an acute hospital; and death.

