### Criteria for discontinuing or modifying allocated intervention in both groups

Therapy sessions will not occur if any of the following conditions are present:body temperature > 37 °C;repeated pain with a numeric rating scale score > 5 (no pain relief during adjusted training);> 16 points of Borg’s rating of perceived exertion scale in two training sessions;a decline in performance of 30% in two following therapy sessions;rehabilitation team perception that therapy is not appropriate despite absence of the above criteria;refusal of consent;decreased alertness and compliance cannot be handled by the therapist;or if training is not possible for one week, without the chance to catch up.

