### Adverse event monitoring and reporting

All AEs will be carefully monitored at every level of the study. All AEs are reported immediately to the responsible physician and the research staff is informed of all AEs. The research team will be responsible for data safety and for the confidentiality of recruited patients. The confidentiality of participants will be granted by using pseudonymised ID lists for all recruited patients. All patient data will be maintained and stored confidentially on a separate server.

The trial will be stopped:if there is an important difference in safety between the groups in one direction,if one of the interventions is associated with unexpected excessive adverse effects such as uncontrollable pain or immoderate high points of Borg’s rating of perceived exertion scale, or there are excessive withdrawals;if the study recruitment is unsuccessful (e.g. three months without any recruitment);or if other situations occur that might justify stopping this trial.

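### Non-serious adverse events have no stated recording occasion after a patient stops training or after session 9, so the safety comparison may be incomplete

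*Protocol article*

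**What the plan says.** The Objective section sets out to "assess the safety and the effects of arm strength training in persons with subacute stroke". The section Assessment of safety and adverse events then describes two streams of recording.

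- **Non-serious events.** A list that includes fatigue, pain, a 30% fall in performance and dizziness ends with the statement that "muscle soreness, swelling and decrease in compliance to training will be continuously recorded". The working step that follows is: "After each intervention, the treating physiotherapist will record the presence of AEs".
- **Serious events.** These are tracked while training runs; in addition, "at the final assessment the following parameters will be systematically recorded: cardiovascular or cerebrovascular events; referral to an acute hospital; and death".

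The section Adverse event monitoring and reporting adds that "All AEs will be carefully monitored at every level of the study" and that "All AEs are reported immediately to the responsible physician and the research staff is informed of all AEs".

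The section on criteria for discontinuing or modifying the allocated intervention begins "Therapy sessions will not occur if any of the following conditions are present". The conditions include repeated pain above 5 on the rating scale, exertion above 16 Borg points in two sessions, and a 30% decline in two consecutive sessions.

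**The concern.** The protocol states what is to be asked at t1, and that list leaves out the non-serious harms, including the shoulder pain that the same section links to a high weight load. For those harms the only named recorder is the treating physiotherapist, and the only named occasion is the end of a session. A patient who stops training stays in the intention-to-treat population until t1 but has no further sessions.

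If stopping is more frequent in the high-intensity arm, later non-serious events in that arm have fewer chances of being recorded. A smaller recorded difference could then be read as evidence of safety. The trial is also to be stopped for an important between-group difference in safety, and judging that requires comparable recording in both arms.

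**Working it through.** **1. Occasions stated for non-serious events**

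| Situation | Stated occasion | Stated recorder |
|---|---|---|
| After an attended session | Yes | Treating physiotherapist |
| Between sessions 1 to 9 | None explicit, though the next session can pick it up | Same |
| After session 9, up to t1 | None | None |
| After a patient stops, up to t1 | None | None |

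The continuous-recording sentence and the monitoring sentence fill none of the empty cells, because they name neither an occasion nor a recorder. Immediate reporting to the physician is a route for events already noticed. It is not a scheduled enquiry.

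**2. Could stopping differ by arm?** The safety section equates 80% of the one repetition maximum with 16 Borg points and 40% with 10 points. The condition for withholding sessions is more than 16 points in two sessions. The high-intensity arm is thus expected to train at the threshold (16 − 16 = 0 points below it) and the low-intensity arm well under it (16 − 10 = 6 points below). Unequal stopping is plausible from the protocol's own figures, but its size is not given.

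**3. Illustration of size.** The protocol gives no figure for stopping or for event rates, so there is none to reproduce. The inputs from the protocol are 9 sessions and 39 patients per arm. Four assumptions are mine:

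- recording takes place only at attended sessions;
- the stopping probability per session is constant;
- the true event rate per session slot is the same in both arms and continues after stopping;
- 5% of the low-intensity arm stop before session 9.

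Let D be the proportion stopped before session 9. Then:

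- stopping probability per session: s = 1 − (1 − D)^(1/8)
- expected attended sessions: S = Σ (1 − s)^k for k = 0 to 8
- ratio of recorded events, high/low: S(high) / S(low), when the true ratio is 1

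| D, high arm | S(high) | Share of 9 | S(low), D = 5% | Ratio |
|---|---|---|---|---|
| 5% | 8.77 | 97.5% | 8.77 | 1.00 |
| 10% | 8.54 | 94.9% | 8.77 | 0.97 |
| 20% | 8.07 | 89.7% | 8.77 | 0.92 |
| 30% | 7.58 | 84.2% | 8.77 | 0.86 |

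**4. Cross-check.** Suppose instead that all who stop do so halfway:

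- full schedule: 39 × 9 = 351 occasions
- high arm, 20% stopping: 39 × (0.8 × 9 + 0.2 × 4.5) = 316
- low arm, 5% stopping: 39 × (0.95 × 9 + 0.05 × 4.5) = 342
- ratio: 316 / 342 = 0.92, as above

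**The case against.** The strongest reply is that the protocol nowhere says recording ends when training does. It says the listed events are recorded continuously and that all events are monitored throughout. A condensed article may leave the exact window to the full protocol. The graphic of Fig. 2, which carries the data collection schedule, was not available to me. This stands as far as it goes: a reader might infer that most events are recorded only after attended sessions and that observation then ceases, but the text does not state that. What remains is narrower. The article does state a t1 safety list, and non-serious events are not on it.

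A reader might also infer that the comparison loses the very patients who matter most. The protocol does not support this. Pain must be repeated, and the decline must occur in two consecutive sessions, so the trigger would normally be recorded before training stops. In a patient-level analysis that patient already counts for that event. Some of the conditions are transient, and cancelled sessions are to be made up. Serious events are covered to t1. Adherence and drop-out are recorded, so unequal stopping would be visible.

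The gap after session 9 applies to both arms and should be short, since the abstract places t1 immediately after the three weeks of therapy.

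A much larger loss can be constructed. With assumed true rates of 30% and 15%, and one third of high-arm events unseen, the observed rates become 20% and 15%, and two thirds of the difference disappears. That result rests on an arbitrary loss in one arm only and does not follow from the 316 and 342 occasions above.

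One counter-argument carries less weight. The planned 5% dropout does not limit stopping, because a patient can stop training and still be measured at t1.

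**Conclusion.** The point holds as a gap in ascertainment, not as a demonstrated bias. Non-serious events after session 9, or after a patient stops training, have no stated collection occasion, and the two adverse-event sections do not settle the matter between them. Because the conditions for withholding sessions overlap with the adverse-event list, and expected exertion differs by arm relative to the threshold, under-recording could favour the high-intensity arm.

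The size is unknown. Under the assumptions above, the ratio of recorded events falls from 1.00 to about 0.92 with 20% against 5% stopping, and there is no distortion from stopping if it is equal in both arms. The figure concerns event counts. It would be smaller if load-related events become rarer once training stops, and smaller for patient-level proportions where the triggering event is already recorded. This is a cheap improvement worth making, and it does not call the design into question.

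**What to change.** Reconcile Assessment of safety and adverse events with Adverse event monitoring and reporting by stating the observation window for non-serious events as t0 to t1 for every randomised patient. At t1, ask all of them, including those who stopped training, about the full event list since the last recording, alongside the serious events already collected there. To protect blinding, ask after the outcome tests or have someone other than the blinded assessor ask. Report, by arm, the proportion of randomised patients with each event from t0 to t1.

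The cost is one checklist at an existing visit. There is a small unblinding risk, which the ordering or the separate questioner avoids. Reported event rates may be higher than under the present wording. No treatment rule changes.

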### Randomisation and concealment of allocation

Each study participant will be randomly assigned to one of two intervention groups, either the low-intensity training group or the high-intensity training group. Allocation will be concealed within an opaque sealed envelope. The computer-generated random allocation sequence list will be carried out using a random-number generator (randomizer.org). Assignments will be enclosed in sequentially numbered, opaque, sealed envelopes and stored at the central study centre. The persons who assess eligibility, obtain informed consent and enrol patients in the trial (SH, CH) have no knowledge of group assignment (Fig. 2). After recruitment and after the initial assessment, the appropriate numbered, opaque, sealed envelope will be opened and the randomisation information will be given to the patient and therapists (but not to the outcome assessors). We will not include further potential covariates in our stratification. However, we will test the influence of different covariates statistically on the main effect of the primary outcome.

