### Low-intensity training group

The workload in the low-intensity training group will be 40% of 1RM, examined at the beginning of the first training session. Participants will also do three sets of an increasing number of repetitions of each exercise. In the first training session, they will perform ten repetitions, one more in each following training session, with up to 18 repetitions in the final training session according to Table 3. The resistance will not be changed.

We chose a low-intensity progressive training to compare two true active and potentially effective interventions. One intervention increases by weight and the other by repetitions. This low intensity was often used in therapeutic studies for stroke patients [14, 42].

If the grasp of the objects is not possible, a wrist cuff can be used to fix the grip. The therapists will document ROM, repetitions and intensity for each exercise in each session. If a training is cancelled (because of illness or other liabilities), it will be repeated as soon as possible.

The therapy session will be adjusted, interrupted or terminated if the patient (using continuously monitoring):has pain with a numeric rating scale score > 5;has a body temperature > 37 °C,has > 16 points of Borg’s rating of perceived exertion scale;or has a decline in performance of 30%.

The adherence of the training programme will be documented and reported. All single exercises in the arm training programme are well-known and used routinely under different circumstances for the target patients in our clinic. Our additional training programme with systematically augmented exercises is, however, not described in the medical literature yet. For this reason, we underwent a pilot training programme testing the feasibility of the arm training programme in our clinic with all above-mentioned criteria. In five patients, we found that this pilot training programme might be feasible without any AEs.

Both groups will be supervised by one of two experienced physiotherapists not involved in assessment. To control for co-interventions (standard therapy for the upper limb) during the intervention phase of the study (t0 to t1), we will extract information of the total duration and content of both standard and additional therapy from the daily and weekly documentation of our clinic. Content will be described for each 10-min block.

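### Adverse events are recorded by the treating physiotherapist, who knows the arm, so arm-dependent recording can bias the between-arm comparison for events that depend on asking or judgement

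*Protocol article*

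**What the plan says.** **Who records.** Under Assessment of safety and adverse events, "After each intervention, the treating physiotherapist will record the presence of AEs".

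**What that person knows.** Under Randomisation and concealment of allocation, once the envelope is opened, "the randomisation information will be given to the patient and therapists (but not to the outcome assessors"). Under Low-intensity training group, "Both groups will be supervised by one of two experienced physiotherapists not involved in assessment".

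**What is blinded.** The abstract's Methods paragraph says "We will measure primary and secondary outcomes with blinded assessors at baseline and immediately after three weeks of additional therapy". Adverse events are not among the endpoints listed under Outcome measures.

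**What is recorded.** The list begins with "AEs such as self-reported fatigue, a decline in performance of 30%, pain, dizziness, amentia or impaired consciousness" and ends with "swelling and decrease in compliance to training will be continuously recorded". Vascular events, referral to an acute hospital and death are recorded as well, during the intervention phase and at the final assessment; the article does not say by whom.

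**What rests on it.** The abstract says "The aim of this study is to investigate safety and effectiveness of arm strength training in subacute stroke patients", and the Objective repeats safety alongside effects. The abstract's Discussion promises "robust evidence for effects and safety of high-intensity arm training". Under Adverse event monitoring and reporting, an important one-directional safety difference between the groups is a reason to stop the trial.

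**The concern.** The blinding that protects the efficacy outcomes does not reach the safety data. The recorder delivers the training, knows the load, and works under a protocol that names strain and shoulder pain as a risk of high weight. A therapist who expects trouble in the heavy arm may look harder for it there. One who believes in the heavy training may play the same complaint down. In either case the difference between arms mixes true risk with the recorder's knowledge of the arm.

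This matters more here than in many trials. The Background says that adverse events in the subacute phase have not been examined, so the trial offers its safety comparison as new evidence. The article also criticises earlier work in this population for unblinded assessors.

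**Working it through.** The article gives neither an adverse-event rate nor a recording rate. The check therefore sets the text out first and then illustrates the size on assumed figures.

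**1. Exposure of each type of event**

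| Type of event | How it comes to be recorded | Exposure to the recorder's knowledge |
|---|---|---|
| Decrease in compliance, swelling | Therapist's judgement or inspection | Direct |
| Fatigue, pain, dizziness, soreness | Patient's report, noted as present by the therapist | Through how actively it is asked and what is noted |
| 30% performance decline | Numeric threshold; repetitions, intensity and range of motion are documented for each exercise and session (Low-intensity training group) | Limited, because it can be checked |
| Vascular events, acute-hospital referral, death | Clinical events; recorder not named | Little |

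**2. Group size.** The plan's own figure reproduces. The difference is 10 − 8 = 2 kg and the SD is 3 kg, so the standardised difference is 2/3. With two-sided 5% (two-sided is an assumption) and 80% power, the exact two-sample t test gives 36.3, so 37 per arm (power 0.808). Then 37 / 0.95 = 38.9, so 39 per arm and 78 in total. Only the 39 per arm is used below.

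**3. Apparent risk under unequal recording (assumed rates).** Observed risk = true risk × proportion recorded. Take a true risk of 30% in both arms:

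- High-intensity arm, 90% recorded: 0.30 × 0.90 = 0.27
- Low-intensity arm, 75% recorded: 0.30 × 0.75 = 0.225; ratio 0.27 / 0.225 = 1.2
- Low-intensity arm, 60% recorded: 0.30 × 0.60 = 0.18; ratio 0.27 / 0.18 = 1.5

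Swapping the arms reverses the direction: 0.18 / 0.27 = 0.67.

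**4. Chance of a significant difference with no true difference.** This uses Fisher's exact test at 5% with 39 per arm. The article names no test for adverse events, so the choice is an assumption.

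| Recorded, high v low | True risk 30% | True risk 50% | True risk 70% |
|---|---|---|---|
| 80% v 80% | 3% | 3% | 3% |
| 90% v 70% | 6% | 10% | 18% |
| 90% v 60% | 11% | 20% | 38% |
| 95% v 50% | 23% | 45% | 75% |

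In the two middle rows the observed risks differ by 6 points (0.30 × 0.20) to 21 points (0.70 × 0.30).

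**5. Nine recording occasions.** If an event is recorded in 5% v 2% of sessions, independently between sessions, the share of patients with at least one is 1 − 0.95⁹ = 37% v 1 − 0.98⁹ = 17%. Fisher's test is then significant in 44% of trials. Here too the per-session rates are assumed.

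**The case against.** **The recorder cannot be blinded, and is needed.** A physiotherapist who sets the load knows the arm, and recording at each session by that person serves patient care. This stands: the therapist's record must be kept. It does not make that record a blinded comparison.

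**Much of the list is not the therapist's judgement.** Fatigue is self-reported, pain is rated on a numeric scale elsewhere in the article, and the 30% decline can be checked against documented loads and repetitions. This stands and narrows the point. A reader might infer that the whole list is subjective; the text does not support that.

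**The Borg figures are not an instruction to expect harm.** A reader might take the values of 16 at 80% and 10 at 40% of the one-repetition maximum as priming the therapist. They are given as an example for monitoring intensity, and Borg ratings are not on the adverse-event list. The support for a prior expectation is the separate sentence on strain and shoulder pain.

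**The same two physiotherapists serve both arms.** Differences in habit between therapists are therefore not built into the comparison. This stands. What remains is different recording by the same person according to arm.

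**Question wording may be in a case report form.** It may, and its absence from the article is no fault. But the article itself settles who records, and settles on someone who knows the allocation.

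**Blinded questioning would not give an unbiased comparison.** Patients are told their arm, so expectation can colour self-reports whoever asks. This stands, and it is why a blinded interview should support the session log and not replace it.

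**Conclusion.** The concern holds for events that depend on asking or judgement: fatigue, pain, soreness, dizziness, swelling and decrease in compliance. Their recorder knows the arm, the article states a risk tied to high load, and the comparison feeds both a stated aim and a stopping criterion.

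A reader might go further and infer that the safety results will be biased against high-intensity training, or that a false significant difference is likely. The article supports neither. It shows that bias can arise; it gives no means of deriving the size or direction. The apparent ratios of 1.2 and 1.5 rest entirely on assumed recording rates. Under the assumed rates the chance of a false significant result runs from 6% (90% v 70% recorded, true risk 30%) to 75% (95% v 50%, true risk 70%), against about 3% with equal recording. Moderate differences in recording more often shift the observed rates without reaching significance.

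Vascular events, acute-hospital referral and death are little affected. The blinded grip-strength endpoint and the sample size are not touched. This should be changed because safety is a stated aim and the change is cheap; it does not threaten the primary analysis.

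**What to change.** 1. **Session log as the main record.** At each session, put the existing adverse-event list to every patient as fixed, patient-rated questions, worded identically in both arms. Keep this contemporaneous log as the main adverse-event record and report it as collected unblinded.
2. **Derive the 30% decline.** Calculate it from the documented loads and repetitions by one written rule for both arms. The rule has to cope with progression by weight in one arm and by repetitions in the other.
3. **Supporting comparison at t1.** Have the existing blinded assessor ask the same scripted list after all outcome tests are finished and after the assessor's allocation guess for that patient is recorded. Report the result beside the log. This order protects both the tests and the blinding check; the guess, now placed after the end of the study period, would need to be fixed at this point in the visit.
4. **Wording.** Limit the abstract's safety claim to what unblinded recording in patients who know their arm can support.

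**Cost.** A few minutes per patient, at sessions and a visit that already take place with staff already there. The t1 interview relies on three-week recall, in a sample that includes people with mild aphasia. A patient may disclose the arm during it, and reporting bias from the patient's own knowledge remains.
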